# The effect of side-alternating vibration therapy on mobility and health outcomes in young children with mild to moderate cerebral palsy: design and rationale for the randomized controlled study

**DOI:** 10.1186/s12887-020-02377-2

**Published:** 2020-11-05

**Keywords:** Cerebral palsy, Vibration therapy, Bone density, Mobility, Gross motor function, Body composition, Muscle function, Respiratory function, Quality-of-life

## Abstract

**Background:**

Cerebral palsy (CP) is the most common cause of physical disability in early childhood. Vibration therapy (VT) is a promising rehabilitation approach for children with CP with potential to impact mobility, bone and muscle health as demonstrated by extant research. However, it is still unclear how long therapy must be conducted for and what the optimal vibration frequency is in order to gain health benefits.

**Methods/design:**

The study is a randomized clinical trial evaluating and comparing the effects of two vibration frequency (20 Hz vs 25 Hz) and duration protocols (12 weeks vs 20 weeks) of side-alternating VT on mobility and other health parameters in children with CP. Children aged 5–12 years old with CP and GMFCS level I-III who are able to understand instruction and safely stand are eligible for the study. Exclusion criteria include bone fracture within 12 weeks of enrolment; acute conditions; the history of significant organic disease; the history of taking anabolic agents, glucocorticoids, growth hormone, and botulinum toxin injection into lower limbs within 3 months of enrolment. All participants will act as their own control with a 12-week lead-in period prior to intervention. The intervention period will consist of 20 weeks of home- or school-based VT 9 min per day, 4 times a week. After the baseline assessment, participants will be randomized to either a 20 Hz or 25 Hz vibration-frequency group. The primary outcome is mobility measured by a 6-min walking test, with analysis performed on the principle of intention to treat. Secondary outcomes include body composition, muscle strength, physical activity level, balance, gross motor function, respiratory function, and quality of life. Participants will undergo four assessment visits over the study period: baseline, at weeks 12, 24, and 32.

**Discussion:**

The results of the study will provide evidence-based insights into the health benefits of side-alternating VT as a therapeutic tool in young children with cerebral palsy. The investigation of different vibration training protocols will help define the optimal parameters of intervention protocols (duration, frequency) of side-alternating VT to maximize outcomes on the health of 5–12-year-old children with CP.

**Trial registration:**

Australian New Zealand Clinical Trials Registry (ANZCTR): 12618002026202 (Registration date 18/12/2018).

## Background

Cerebral palsy (CP) is a group of disorders of the development of movement and posture, causing activity limitation attributed to non-progressive disturbances that occurred in the developing fetal or infant brain [1] with the estimated prevalence of 2 per 1000 children [2, 3]. The most common characteristic of CP is a motor impairment that embraces reduced mobility, impaired motor skills, changes in muscle tone and strength, restricted range of motion, and deterioration of balance and gait [4]. Improving mobility and functional activity is one of the main therapeutic goals for children with CP [5]. Given the key factors contributing to impaired mobility are muscle weakness and spasticity [6–8], current therapies of children with CP include orthopedic surgery, antispastic drug therapy, and a variety of muscle strength rehabilitation tools [9, 10]. However, these interventions are time- and cost-consuming, complex, and require specialized equipment and/or professional staff [11–13].

Vibration therapy (VT) was introduced about 20 years ago as a prospective rehabilitation approach for children and adults with CP. VT is well tolerated by children with CP with no serious adverse effects reported [14–18]. The most frequently described side effects include temporary redness and itchiness of the leg skin that has an adaptive effect [17, 19, 20]. To date, only one study has reported fatigue and pain as a reason of discontinuation single vibration sessions in fewer than 1% of training sessions with no evidence that these effects had been caused by vibration training [21]. VT has been found to be an effective and cost-efficient method to improve muscle strength [15, 17], decrease spasticity [17] and, consequently, improve mobility [16, 17, 21] in this population. In addition, previous studies have reported VT to be effective in improving muscle function [16, 17, 22], bone mineral density [16, 22, 23], gross motor function [17, 22], as well as the quality of life [16] in children and young adults population. A recent review by Ritzmann et al. (2018) that appraised 28 published studies on the effects of VT on functional, neuromuscular and structural parameters of patients with CP revealed an emerging collective evidence that speaks to the potential of VT in ameliorating the symptoms of the disease in both short term (i.e., reducing reflex excitability, spasticity, and coordination deficits) and long term (i.e., improving movement ability, increasing muscle mass and bone mineral density) [24]. However, despite the promising results demonstrated by VT, its wider application is limited by the heterogeneity of methodological approaches used in extant research, with protocols varying in frequency and duration, which complicates the interpretation of the results and the development of treatment protocols [15, 17, 21–23, 25, 26]. In the reported longitudinal studies, the duration of the vibration training varied from 3 to 24 weeks and the target frequency of the vibration stimuli ranged from 18 to 25 Hz [24]. To our knowledge, there have been no published studies that compared the effect of different duration and frequency parameters of side-alternating vibration therapy on the health outcomes of children with CP in longitudinal studies. Therefore, it is still unclear whether higher intensities and/ or longer interventions will bring more health benefits or not. As summarized in the aforementioned systematic review of extant research on the effectiveness of VT, “while the success of VT has been outlined clearly … systematic judgment on the choice of VT parameters requires further investigation” ([24], p. 1623).

Available studies have also reported a diverse range of outcomes [15, 17, 22, 23, 25, 26], which complicates the comparison of the available data across studies. To date, the only study with a comprehensive set of assessment has been published by Gusso et al. (2016) and involved adolescents and young adults with cerebral palsy. The study found a positive effect of 20 weeks of side-alternating VT on mobility, muscle mass and function, bone mineral density as well as the quality of life [16]. The findings were, however, limited to the adolescent population and cannot be generalized to younger children due to the known impact of age, growth speed, puberty and sex hormone status on the muscle and bone health, development, and mobility level [27–30]. Therefore, in designing the study and selecting the assessment tools, we sought to conduct a robust assessment that would provide a comprehensive insight into the effectiveness of VT on the health of children 5–12 years old with CP (i.e., muscle function, muscle strength (isometric and dynamic), and bone health) and to evaluate the effect of different parameters of VT on this population.

Apart from the musculoskeletal involvement, children with CP may present with multiple medical conditions, including compromised respiratory function, which affects the quality of life, hospitalization frequency, and life expectancy [31–34]. As shown in previous research, respiratory muscle weakness and poor cough both contribute to respiratory impairment in children with CP [35–37]. To our knowledge, no studies have explored the impact of VT on respiratory function in children with CP. Available studies were conducted in the adult population with chronic obstructive pulmonary disease [38, 39]. We hypothesize that VT has the potential to improve respiratory function by improving the strength of diaphragm and core muscles which play an important role in the breathing cycle and respiratory function [37, 40, 41].

Therefore, our study proposed to examine and compare the effect of two frequency and duration protocols of side-alternating vibration therapy on mobility, muscle and bone health, motor function, as well as respiratory function and well-being in young children 5–12 years of age with mild to moderate CP.

## Methods

### Study design

The study is designed as a randomized clinical study, where all participants will act as their own control, with a 12-week lead-in period prior to the intervention (Fig. 1). For the intervention part of the study, participants will be randomized into two groups varying in the frequency of vibration stimuli. The study was approved by the Health and Disability Ethics Committee (Ministry of Health, New Zealand; 19/NTB/2), and was registered with the Australian New Zealand Clinical Trials Registry (ANZCTR: 12618002026202). Institutional approval has been obtained from the Auckland District Health Board (ADHB).

**Fig. 1 Fig1:**
[figure not shown]
Study design. **a** Study flow diagram. **b** Study design scheme

### Participants

Children aged 5–12 years with any type of cerebral palsy and a GMFCS classification level I-III (very mild to moderate) are eligible for the study. Participants need to be able to understand and follow protocol instructions and safely stand on the vibration platform. Exclusion criteria include a bone fracture within 12 weeks of enrolment; acute thrombosis, tendinitis, nephrolithiasis, discopathy or arthritis; history of clinically significant organic disease; history of taking anabolic agents, glucocorticoids or growth hormone for at least 1 month within 3 months of enrolment; and a history of botulinum toxin injection into lower limbs within 3 months of enrolment.

### Recruitment

Potential participants will be identified from the ADHB database using the described exclusion/inclusion criteria (Fig. 1a). Those who fit the eligibility criteria will initially be approached by pediatricians, nurses or physiotherapists with a short explanation and flyer of the study. School physiotherapists at satellite schools in the Auckland area will also be notified about the study and will be able to inform prospective participants. Self-referrals will also be accepted. Once parents/caregivers of a potential participant have indicated an interest in participating, they will be contacted by a member of the research team to provide a detailed explanation concerning the study design, assessment tests, and vibration therapy. A participant information sheet will then be sent by email or regular mail. Two-five days later, the researchers will contact prospective families to answer any questions, and if a family agrees to participate, the initial appointment will then be scheduled.

### Randomization

Randomization will be performed immediately after the initial assessment using an online random number generator available at https://www.randomizer.org. Participants will be allocated to either group 1 (VT frequency 20 Hz) or group 2 (VT frequency 25 Hz). The same member of the research team will enrol participants and assign them to the intervention group. Given that the current study is part of a PhD project, all the procedures (i.e., randomisation, testing, VT sessions) will thus be run by the same member of the research team, making the blinding of the researchers unfeasible in this study. Additionally, the vibration frequencies produced by the Galileo™ vibration platform are readily observable by both researchers and study participants, which makes it unfeasible to ensure blinding not only at the randomization but the intervention stage as well.

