### Control period

The control period will start immediately after the first assessment visit and will last 12 weeks (Fig. 1a). During the control period, participants will continue their usual activities and care.

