### Intervention

Following the control period, a 20-week intervention period will start. It will consist of 4 vibration sessions a week performed on Galileo Basic vibration plates (Novotec Medical, Pforzheim, Germany). Participants will start from three 1-min bouts of vibration training at the frequency of 12 Hz with a gradual increase of both frequency and duration over the first 4 weeks to achieve the target frequency and time (3 sets of 3 min vibration training alternating with 3-min breaks between them). The target frequency of the vibration will vary depending on the intervention group (either 20 Hz or 25 Hz) and will be maintained for the remainder of the intervention period. Other parameters will be kept comparable in both treatment groups: amplitude – 2-4 mm, acceleration – maximum 11.4 g. Participants will stand barefoot on the plate with knees slightly bent, back straight, and arms free. For participants with poor balance, an adjustable metal frame will be used for safety purposes.

The vibration therapy frequencies (20 Hz vs 25 Hz) have been selected based on current literature and the Galileo vibration platforms manufacturing specifications. According to the latter, the main effect of low frequencies (12–20 Hz) lies in an improvement of muscle function and coordination whereas high frequencies (more than 20 Hz) have an impact on muscle power and muscle force [42]. According to the literature, 20 Hz is a typically recommended frequency for children with cerebral palsy [43]. In addition, 20 Hz has been shown to be the safest of low frequencies due to low vibration transmissibility to the head [19] and better coordination and posture stabilisation during the vibration training sessions [44]. 25 Hz was chosen as it is the highest frequency that has been used in long-term studies of side-alternating vibration training that involved children with cerebral palsy and that has demonstrated no severe adverse effects [24]. To summarize, the two frequencies were selected since they provide the optimal combination of expected results, as informed by extant literature and equipment specifications, and adherence to the ethical obligation of not compromising the patients’ safety.

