#### Data analyses

The data will be entered into an Excel workbook on password-protected computers, and later exported into SPSS v25 (IBM Corp, Armonk, NY, USA) and SAS v9.4 (SAS Institute, Cary, NC, USA) for statistical analyses. Baseline demographic and clinical characteristics of participants will be summarised by trial group allocation. Treatment evaluation of the primary outcome (i.e. mobility or distance covered during the 6-min walk test) will be performed on the principle of intention to treat, using data collected from all randomised participants. Data will be analysed using random effects mixed models with repeated measures, to account for the non-independence of measurements on the same participant. Models will incorporate as fixed effects the trial group allocation (20 vs 25 Hz), time-point (assessment II, III, or IV), and their interactions as fixed effects, as well as the participant’s GMFCS level; in addition, the baseline value of the outcome variable will be included as a covariate. There will be no imputation of missing data, as based on our previous studies, we expect very limited or no loss to follow-up. Nonetheless, for a small subset of secondary outcomes, such as certain functional tests on the Leonardo platform that cannot be performed by participants with GMFCS level III, only subgroup analyses will be carried out including solely participants with GMFCS level I-II. Model-adjusted differences between randomization groups and within groups (including the potential effects of treatment duration) will be calculated and reported with 95% confidence intervals. All statistical tests will be two-sided at *p* < 0.05, without adjustments for multiple comparisons.

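### Allocation is generated 12 weeks before any vibration, so the T1 assessor knows each child's frequency and lead-in losses count as randomised children

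*Protocol article*

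**What the plan says.** All references are to the protocol article.

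- **Timing of allocation.** The Randomization section says "Randomization will be performed immediately after the initial assessment". The abstract agrees: "After the baseline assessment, participants will be randomized to either a 20 Hz or 25 Hz vibration-frequency group".
- **Lead-in.** The Control period section says "The control period will start immediately after the first assessment visit and will last 12 weeks", and "During the control period, participants will continue their usual activities and care". Nothing in it differs by group.
- **Start of treatment.** Under Intervention, vibration begins after the control period, at 12 Hz for every child, "with a gradual increase of both frequency and duration over the first 4 weeks to achieve the target frequency and time".
- **Blinding.** The Randomization section gives two reasons against it. One person carries out randomisation, testing and training, "making the blinding of the researchers unfeasible in this study". In addition, the platform's frequency can be perceived by anyone present.
- **Analysis.** Under Data analyses, the primary evaluation "will be performed on the principle of intention to treat, using data collected from all randomised participants". The mixed model takes assessments II, III and IV (T1, T2, T3) as outcome time-points, with group, time and their interaction, GMFCS level, and the baseline value as covariate. Missing data are not imputed.

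**The concern.** An allocation is normally generated as late as practicable, just before the groups begin to be treated differently. Here it exists for at least 12 weeks in which it has no function, and the article gives no reason for that order.

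Two things follow. First, the T1 assessor knows the group although nothing requires it. The 6-minute walk depends on effort, and the assessor gives encouragement. Standardised wording reduces the scope for influence but does not remove it. The Discussion rests the own-control design on within-subject comparison of a control period with an intervention period, and T1 is the end of one and the start of the other. An error at T1 that differs by frequency would therefore enter both changes with opposite signs. It would also appear as a group difference at T1 in the primary model, before any treatment difference exists.

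Second, a child who leaves during the lead-in belongs to the randomised set but can contribute nothing to the primary model.

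**Working it through.** **1. Time between allocation and any difference in treatment.** Follow-up is 12 weeks of control plus 20 weeks of intervention, 32 weeks in all. Allocation comes at week 0 and vibration after week 12, so 12/32 = 37.5% of follow-up precedes treatment. Both groups start at 12 Hz and build up over 4 weeks, so the groups separate at some point between weeks 12 and 16. Twelve weeks is therefore a minimum.

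**2. Do the stated reasons against blinding cover T1?**
- One person randomises, tests and trains. That person cannot know an allocation that has not yet been generated.
- The frequency is perceptible on the platform. No child trains on a platform before T1.

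Neither reason applies at T1. With allocation after T1 testing, two of the four visits (T0 and T1) are assessed without knowledge of frequency, instead of one, and no extra staff are needed.

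**3. What a frequency-dependent shift at T1 would affect.** Suppose T1 is shifted by x in one group only.
- Control-period change (T1 − T0) in that group moves by +x.
- Change on vibration (T2 − T1 or T3 − T1) moves by −x.
- The own-control contrast, change on vibration minus control change, moves by −2x.
- The between-group difference in change from T1 moves by x in absolute size.
- The model's between-group difference at T2 or T3 does not move. A shift common to one group at T1 is absorbed by the group-by-time term for T1, and the covariate is the baseline value, which Clinical assessments labels T0 and which is measured before randomisation.

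The documents give no basis for a value of x, so none is assumed.

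**4. The plan's sample size.** Inputs from Sample size: 44 children, 10% drop-out, final total 48 (24 per group). 44/0.9 = 48.9 and 44 × 1.1 = 48.4. By group, 22/0.9 = 24.4, rounded up to 25, or 50 in total. The stated 48 is within two of each, so no arithmetic error is alleged.

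**5. Children randomised and lost before T1.** The plan does not say when losses fall, so this is an assumption.
- Even spread over 32 weeks: 48 × 0.10 × 12/32 = 1.8 children.
- Constant hazard: 1 − 0.9^(12/32) = 0.0387, and 48 × 0.0387 = 1.9 children.
- Range: 0 if no loss falls in the lead-in, up to 48 × 0.10 = 4.8 if all of it does.

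**6. Cost in power.** The 6-minute-walk mean and SD behind the 44 are not given. Back-solving 22 per group at two-sided 0.05 and power 0.95 (t-test) gives a standardised difference of 1.11. At that effect, power is 0.965 with 24 per group, 0.950 with 22 and 0.929 with 20.

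**7. Numbers if allocation follows T1.** Under constant hazard, loss after T1 is 1 − 0.9^(20/32) = 0.064. Then 44/(1 − 0.064) = 47 randomised children give 44 completers, from 44/0.9 = 48.9, about 49, enrolled at T0. Enrolment is practically unchanged.

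**The case against.** The case for leaving the plan alone has real substance.

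- **Expectation about vibration itself is untouched.** Every child receives vibration after T1. An assessor who hopes that it works has the same incentive at T1 whether or not the frequency is known. This stands: later randomisation removes only the part of any bias that depends on frequency.
- **The main randomised contrast does not hang on T1.** The T2 and T3 group differences are adjusted for T0. This stands, and it limits the point to within-group change and to the T1 group comparison.
- **T2 and T3 remain unblinded.** This stands.
- **Losses should be few and unrelated to treatment.** Data analyses expects very little or no loss, and before the groups differ, treatment cannot cause it. This largely stands. However, Sample size itself allows for 10%, and the allowance is not split between lead-in and intervention.

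A reader might also infer that families know their group throughout the lead-in. The article does not say when they are told, and for home training it places the instruction session at the end of the second visit. Only the researcher's knowledge is established.

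None of this gives a reason for randomising at T0, and none makes the arguments against blinding apply at T1.

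**Conclusion.** The point holds as an avoidable weakness in the order of events. The T1 assessor knows the frequency for all children tested, at a visit where this could be avoided at almost no cost. The exposure is a frequency-dependent error in within-group change and in the T1 group comparison. Its size cannot be estimated from the article.

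Lead-in losses come to about 1.8 of 48 children if the planned 10% is spread evenly, with a range of 0 to 4.8. A reader might take this to mean that intention to treat is broken. The documents do not support that: the stated principle is sound, and a few randomised children without outcome data cost mainly precision, which the power figures show to be small. Those figures rest on a back-solved effect, because the plan's own mean and SD are not given.

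It would also go too far to conclude that the frequency comparison at T2 and T3 is biased by this timing, or that moving the allocation would make the trial blinded.

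**What to change.** Generate the allocation after all T1 assessments are recorded and before vibration instruction. For home-based families that instruction already takes place at the end of the second visit, so the new order fits the existing schedule. Define the intention-to-treat set from that point. Report children lost in the lead-in separately; they have T0 data only and so cannot inform control-period change. Children already randomised stay as allocated, and the trial report states the change of timing.

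The abstract, the Randomization section and Fig. 1 need amending. The practical cost is that plates and diaries are assigned on the day of T1 rather than in advance. No change to the eligibility criteria is proposed: they are tied to enrolment, and re-applying them at T1 could alter who may receive vibration, which is a separate matter.

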### Statistical considerations

#### Sample size

The sample size calculation was performed in GPower software version 3.1.9.2. For the calculation, we used the mean and standard deviation obtained in the 6MWT from the clinical trial performed of 40 participants with cerebral palsy [14]. Setting the level of statistical significance at 0.05 and power at 0.95, a minimum size of 44 participants for two groups was found. Considering a 10% drop-out rate, the final sample will include 48 participants in total, with 24 for each intervention group.

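### One unblinded researcher enrols, randomises, treats and tests with no allocation concealment, and a visible frequency does not make concealment unfeasible

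*Protocol article*

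**What the plan says.** The Randomization section of the protocol article places allocation directly after the first assessment, "using an online random number generator available at https://www.randomizer.org". It then states: "The same member of the research team will enrol participants and assign them to the intervention group". Because the trial is part of a doctoral project, "all the procedures (i.e., randomisation, testing, VT sessions) will thus be run by the same member of the research team". It adds that staff and children can see the frequency of the plate, "which makes it unfeasible to ensure blinding not only at the randomization but the intervention stage as well".

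The Sample size section plans 48 children, "with 24 for each intervention group". The Data analyses section puts GMFCS level and the baseline value of the outcome in the model. For a small set of secondary outcomes that level III children cannot perform, "only subgroup analyses will be carried out including solely participants with GMFCS level I-II".

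**The concern.** Blinding and allocation concealment are different safeguards. Blinding keeps the arm hidden after assignment, and a visible vibration frequency defeats it. Concealment keeps the next assignment hidden, and out of the enroller's control, until the child is irrevocably in the trial. It does not depend on what the treatment looks like. The Randomization section carries the argument about visible frequency back to the randomisation step, where it does not apply. The doctoral staffing explains why one person tests and treats. It does not explain why that person must also generate and assign the allocation.

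At stake is the 20 versus 25 Hz comparison, the only one that rests on randomisation. The Intervention section gives a well-meaning researcher a reason to steer: it describes 20 Hz as favourable for safety and posture, and 25 Hz as the highest frequency used in comparable long-term studies. Moving a less stable child towards 20 Hz would be an understandable impulse and would confound the comparison. Adjustment for GMFCS level and baseline removes measured differences only, not selection on posture, motivation or family support. The primary outcome, the 6-minute walk, depends on effort and is done with encouragement from the same team.

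**Working it through.** **1. The planned sizes.** Inputs (Sample size): 44 children for two groups, significance level 0.05, power 0.95, 10% drop-out, final sample 48. The Data analyses section states two-sided tests.
- 44/0.9 = 48.9 and 44 × 1.1 = 48.4. Both round up to 49, so the stated 48 is reproduced to within one child.
- The 44 cannot be checked, because no difference or standard deviation is printed. The standardised difference it implies for 22 per arm is (1.960 + 1.645) × √(2/22) = 1.09 by the normal approximation and 1.11 by the noncentral t. The value 1.11 is used below.

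**2. Two readings of the allocation step.** The article gives the timing and the tool, but not whether each child is drawn singly or a list is prepared.

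| Reading | Position of the enrolling researcher | Route to selection |
|---|---|---|
| Single draw after the visit | Cannot predict the result, but has just assessed the child and makes the draw | Repeating or overriding a draw |
| List made beforehand by the same person | Knows or can look up the next arm | Choosing whom to enrol, or when |

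Neither reading contains a step that takes the allocation out of the enroller's hands.

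**3. Group sizes, only if draws are independent and 1:1 (an assumption).** X ~ Binomial(48, 0.5). P(24:24) = C(48,24)/2^48 = 0.115. Power is from the noncentral t at 1.11.

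| Split | Probability of this split or worse | Power at this split |
|---|---|---|
| 24:24 | (exact split: 0.115) | 96.5% |
| 26:22 | 0.67 | 96.4% |
| 27:21 | 0.47 | 96.3% |
| 28:20 | 0.31 | 96.1% |
| 30:18 | 0.11 | 95.5% |

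Uneven arms would be common under this assumption and would cost little.

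**4. GMFCS III, same assumption.** The number of level III children is not given. With 8, 10 or 12 of 48, the chance that at least 75% of them fall in one arm is 0.29 (6 or more of 8), 0.11 (8 or more of 10) or 0.15 (9 or more of 12). With 10, a split of 7:3 or worse has probability 0.34. Within 24:24, a 7:3 split leaves 24 − 7 = 17 and 24 − 3 = 21 children at levels I-II. The effective size per arm is 2 × 17 × 21/38 = 18.8 instead of 19, a negligible loss.

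**5. What blocking would deliver.** An incomplete last block can leave a difference of at most half its length in each stratum. With blocks of 4 and two strata, the largest difference is 2 + 2 = 4, so 26:22 at worst. With blocks of up to 6 it is 3 + 3 = 6, so 27:21 at worst. The arms stay close to 24:24 without being guaranteed equal.

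Steps 3 to 5 concern balance. They do not measure selection bias, and nothing in the documents allows that to be sized.

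**The case against.** A journal article condenses a fuller protocol, so silence about blocks, strata or envelopes is not an error. That stands for blocks and strata. It does not stand for concealment: the article says who assigns and calls blinding at randomisation unfeasible. A fuller document could add independent allocation only by contradicting that.

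If draws are fresh, the next result is unpredictable and the child has already consented and been assessed, so choosing whom to enrol is ruled out. This also stands, but only on that reading, and repeating or overriding a draw remains possible.

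A reader might infer three stronger points that the documents do not support:
- **That children are drawn one at a time without restriction, so the planned 24:24 is contradicted.** This is a natural reading of the timing and tool, but a list prepared with the same tool is not ruled out, and the planned equal arms fit such a list. The split probabilities hold only under independent draws.
- **That missing GMFCS strata are a serious flaw.** The model already contains GMFCS level and the baseline value, and the restriction to levels I-II touches only a few secondary outcomes.
- **That allocating after the baseline assessment is a fault.** It keeps the baseline measurement free of knowledge of the arm, and the remedy below keeps that order.

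**Conclusion.** The concern holds for concealment. One unblinded person controls the path from enrolment through allocation to outcome measurement, and the reason given for not protecting the allocation step applies to treatment, not to randomisation. On either reading in the table, the 20 versus 25 Hz comparison is open to selection that the analysis cannot remove.

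The size is unknown. The documents do not show that selection has occurred or will occur, only that nothing described would prevent or reveal it. Nor is the whole trial compromised: the comparison of each child's control period with that child's therapy period, which the Discussion presents as the basis of the design, does not depend on how the arms were formed.

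Uneven arms are minor: power stays between 95.5% and 96.5% for splits from 30:18 to 24:24, assuming the effect implied by the stated sample size. The conclusion assumes that the article describes the actual procedure, with no independent holder of the sequence.

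**What to change.** For children not yet randomised:
- Have an existing co-investigator who neither enrols nor assesses generate and hold the sequence, in permuted blocks of varying size, preferably stratified by GMFCS I-II versus III.
- Release each allocation through a database module or sequentially numbered opaque sealed envelopes, only after the child is registered and the baseline data are entered.
- In the Randomization section, separate the two ideas: blinding of treatment is not feasible, whereas concealment of allocation is, and is done as above.
- State in the report how children allocated before the change were allocated, and who held any list.

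Keep GMFCS level in the model. Blocking and strata are a small added benefit; independent control of the sequence is the main gain. The change does not blind the walk test, which remains a separate limitation.

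Cost: by estimate, a few hours' work for the co-investigator and a small amendment, with no extra visits and no extra staff at visits.
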